### Ethics

A certified Medical Ethics Review Committee, The Clinical Research Centre Nijmegen (CRCN), in The Netherlands has approved this study, registered under NL44744.091.13. This ethical approval covers all sites of data collection.

### Procedure

Three large mental health institutions participate in this study. Within these departments, professionals will be asked to participate in this study, and be randomized to either ICPT or CAU. Once a professional is included in the study, his or her patients meeting the inclusion criteria at patient level, will be informed about the study and be invited to participate. This invitation letter (to which a brochure about the research is attached), will be signed by the professional, and sent by the department’s management. Patients who express their willingness to participate may either contact their professional or the research team directly. The research team will then contact them by telephone or email, make an appointment for a face-to-face contact, and send formal information about participating in the study by post. In this face-to-face meeting the researcher will explain the study verbally, and obtain informed consent if the patient is indeed willing to participate.

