### Inclusion and exclusion criteria

Patients between 18–65 years of age with a presence of a non-psychotic psychiatric disorder such as depressive, anxiety and/or personality disorder and/or substance abuse and long-term treatment (>2 years) or high care use (>1 outpatient contact per week or >2 crisis contacts per year or >1 inpatient admission per year) in secondary mental health services will be included. Patients with a psychotic, bipolar I or cognitive disorder (e.g. dementia) and a lack of skill in understanding of, or communication in Dutch language are excluded.

Professionals who have an individual caseload of > 5 patients with a non-psychotic disorder, who are willing to be randomized to either CAU or the experimental ICPT-condition and have not expressed intention to leave the present service between now and 12 months are included. Refer to Figure 1 Participant flowchart for details.

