It is expected that this study will yield results that may well be generalized across everyday mental health care. Since our target population consists of patients who are high care users, who are more willing to participate than patients who receive for example assertive outreach [9], we do not expect high selection bias. There are a limited number of inclusion and exclusion criteria in our trial. Unlike in many other trials, patients who are suicidal, aggressive, or self-harming are welcome to participate. Also, comorbidity as well as substance abuse are no exclusion criteria. To encourage participation by professionals, a tailored training-program was developed, based on their day-to-day work with the participants involved. A limitation of this study is the lack of blinding. Participating professionals will know that they conduct ICPT instead of CAU. Patients will also not be blinded.

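### As written, patients appear to be invited, consented and measured at baseline after their unblinded professional is randomised, and no step conceals allocation from recruiters or patients

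*Protocol article*

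**What the plan says.** The order of events is described only in the protocol article's Procedure section. It begins with the professionals: "professionals will be asked to participate in this study, and be randomized to either ICPT or CAU". Patients come next: "Once a professional is included in the study, his or her patients meeting the inclusion criteria at patient level, will be informed". The invitation letter "will be signed by the professional, and sent by the department’s management". On replies, the text says: "Patients who express their willingness to participate may either contact their professional or the research team directly". The research team then makes contact and arranges a meeting. "In this face-to-face meeting the researcher will explain the study verbally, and obtain informed consent".

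Four other sections bear on the point:

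- **Randomization:** the statistician who generates the sequence is independent of whoever recruits the professionals. Nothing is said about those who invite or enrol patients.
- **Inclusion and exclusion criteria:** eligible professionals have a caseload above 5 and are people "who are willing to be randomized to either CAU or the experimental ICPT-condition".
- **Statistical analyses:** the treatment effect is adjusted for client and professional characteristics, with quality of life as the example.
- **Discussion:** neither professionals nor patients are blinded. In a paragraph on generalising the results, the authors write "we do not expect high selection bias", because high care users are willing to take part.

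**The concern.** Randomising professionals makes the arms comparable at patient level only if the patients who enter do so independently of allocation. If allocation is already known when patients are approached, two things can go wrong.

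First, consent can differ by arm. A professional about to deliver a new structured programme has different reasons to encourage patients than one who continues usual care. A patient offered the new programme also decides differently from one offered more of the same. The characteristics most likely to drive this, such as motivation and readiness to change, are plausibly prognostic for quality of life, and the list of baseline instruments names no scale for either.

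Second, the baseline itself can be affected. The primary outcome (MANSA) is self-rated. The DDPRQ, the HONOS and the professional versions of the STAR, CANSAS and IMR are rated at T0 by the person who may already know the arm or have begun training. Adjusting for such a baseline can remove part of a real effect or introduce a false one.

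At stake is the validity of the primary comparison. A larger sample does not reduce this kind of error.

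**Working it through.** **1. Order of events.** The steps compare as follows.

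| Step | What the article gives | What it leaves open |
|---|---|---|
| Allocation of the professional | Mentioned in the Procedure before any patient step | Date of allocation and of disclosure |
| Patient invitation | After the professional is *included* | Whether *included* means already allocated |
| Consent | By a researcher, face to face | Whether the researcher knows the arm |
| T0 | Listed in Table 1 | Whether it precedes disclosure |
| ICPT training | 4 days over 4 weeks | Whether it starts before or after T0 |

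No patient step is placed before allocation, and no concealment is described at any patient step. A team following this text could recruit and measure every patient with the arm known and still be compliant.

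**2. What the analysis can repair.** The mixed model adjusts for measured characteristics. It cannot remove a difference in unmeasured ones, nor correct a baseline that allocation has shifted.

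**3. How large an error a given bias would cause.** The article gives no bias size, so the shifts below are assumptions. The standard error uses the inputs in the Sample size calculation section: 180 patients (90 per arm), clusters of 5, ICC 0.10, and baseline to follow-up correlations of 0.5 (cluster) and 0.8 (subject).

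- Design effect: 1 + (5 − 1) × 0.10 = 1.4
- Correlation of cluster means: r = (5 × 0.10 / 1.4) × 0.5 + (0.90 / 1.4) × 0.8 = 0.693
- SE = √[(2/90) × 1.4 × (1 − 0.693²)] = √[0.02222 × 1.4 × 0.520] = 0.127 SD
- Type I error under a residual shift b: P(|Z + b/SE| > 1.96)

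| Assumed residual shift b (SD) | b/SE | Two-sided type I error |
|---|---|---|
| 0 | 0 | 5.0% |
| 0.05 | 0.393 | 6.8% |
| 0.10 | 0.786 | 12.3% |
| 0.15 | 1.179 | 21.8% |

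A shift of 0.10 SD is one third of the planned effect of 0.3 (0.10 / 0.3 = 0.33).

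**4. Check of the standard error against the plan's own figure.** With all stated inputs and a two-sided 5% test, the usual formula gives 2 × 174.4 × 1.4 × (1 − 0.693²) ≈ 254 patients, not 180. The planned 36 clusters of 5 appear if only the subject-level correlation is used: 2 × 174.4 × 1.4 × (1 − 0.8²) = 175.8, rounded up to 18 clusters per arm. That is a separate matter. It affects this illustration only through the SE, which on that basis is √[(2/90) × 1.4 × 0.36] = 0.106 SD. The three error rates would then be 7.6%, 15.7% and 29.4%. The 0.127 SD figures are therefore the milder of the two sets.

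**The case against.** The strongest reply is that the order is inferred. The trigger for inviting patients is that the professional is *included*, and the inclusion criterion is willingness to be randomised, which can be met before allocation. The sentence about being asked to participate and be randomised can be read as a request for agreement. The flow chart is not shown in the text available here and may settle the sequence. Nothing dates T0 or training relative to allocation. This stands: a reader might infer that the protocol states that baseline follows randomisation, and it does not.

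It is also fair that the professional's documented role is small. Management sends the letter, it goes to the professional's eligible patients, and a researcher explains the study and takes consent. A reader might infer from the caseload minimum above 5 and the target of 5 per cluster that professionals hand-pick their patients. No section describes such picking. But a signature and a reply route still leave room for influence, and the patient's own knowledge of the arm needs no help from the professional.

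The Discussion's remark on selection bias is mainly about generalisability, so it should not be read as a failed rebuttal of differential recruitment. It simply does not cover that question.

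Finally, the assumed shifts come from no source in the article. They show sensitivity to a bias and are not evidence of one.

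**Conclusion.** The point holds in a limited form. As written, the plan permits, and most naturally implies, recruitment and baseline measurement after an unblinded professional has been allocated. It describes no safeguard that keeps allocation from those who invite, those who enrol, or the patients. Mailing to all eligible patients and consent by a researcher reduce the risk without removing it, and baseline adjustment cannot fully correct what remains.

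The size of any bias is unknown. A residual shift of 0.05 to 0.15 SD would take the two-sided type I error to about 7% to 22%. This assumes an SE of 0.127 SD, a normal approximation, 180 analysed patients, and a shift that remains after adjustment. The documents do not support the stronger conclusion that the trial is biased, or that the post-allocation order is confirmed. If allocation is already withheld until T0 is complete, one sentence saying so resolves the matter.

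**What to change.** Rewrite the Procedure section so that the order is fixed for each consenting professional:

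1. Draw up and freeze the list of eligible patients.
2. Invite all of them, with replies going to the research team only.
3. Obtain consent and complete every T0 rating: patient, researcher and professional.
4. Only then disclose that professional's allocation and start ICPT training. Where group training requires it, do this in batches per department or site.

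Report the numbers invited, consenting and refusing by arm, so that readers can judge whether recruitment differed.

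No extra patients or staff are needed. The cost is later training dates, since a batch waits for its slowest recruiter, and a somewhat longer gap between T0 and the start of the intervention. The change cannot be made once recruitment is complete.

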### Treatment integrity

Treatment integrity in the experimental condition will be monitored and discussed by means of supervision. Since there is no clear treatment guideline for CAU, treatment integrity will not be monitored in the control group. Randomly selected audiotapes of treatment sessions will be evaluated by independent raters (Master-level students familiar with ICPT) masked to treatment condition. They will assess whether the tape is CAU or ICPT, and to which extent ICPT-elements are indeed used. The ICPT-professionals assess the ICPT-form and the attached scoring form after each session [9].

### Treatments

#### ICPT

Apart from various specific methods, the focus of ICPT very much lies on the participation of patients through attention for the interaction between patient, professional and social system. The match between patient and professional is highly important for the future course of the care process [17]. In ICPT, the patient is strongly encouraged to take responsibility for his or her recovery. Likewise, in the ICPT-training the professional is taught not to present him or herself as the all-knowing expert, but rather as a facilitator – yet within a clear frame and structure.

A number of stages were conceptualized in the intervention program, each fitting an important step in the theoretical model, resulting in three stages that fit the patient’s level of acceptance of help and cooperation. Apart from these stages (described in detail below), we concluded that an intervention for this patient group program should focus on: (1) a clear generic treatment structure (to prevent uninformed and haphazard low-dosage help), (2) a phased model (which fits the patient’s level of acceptance of help), (3) a therapeutic style that fits the phase the patient is in, (4) a routine monitoring of the interpersonal contact between patient and professional, and (5) support for team professionals [18].I.**Generic structure:** Based on various evidence-based treatments of specific non-psychotic disorders [19,20], we introduced a fixed structure for each session, taking 45 minutes as the standard duration. The first 5 minutes are used by the professional and the patient to set a mutually agreed on agenda for the session. The next 5 minutes are used to look back from the current to the previous session. In the following 25–30 minutes the themes set on the agenda, are discussed and summarized. The last 5 minutes are used to look back on the session and to fill out a report form (professional) and a feedback form (patient).II.**Stage model:** In the stage model patients may move from the 1st stage (optimization of working alliance), through the 2nd stage (clarification of an agreement on goals and tasks) to the 3rd stage (improvement of psychiatric and social functioning). In order to optimize the patient-professional interaction across all stages, it is crucial for the professional to determine in which stage the treatment contact is located. The stage model helps professionals to structure their treatment, using different methods across different stages.III.**Therapeutic methods per stage:** One of the crucial elements of ICPT, in order to prevent ineffective illness behaviour and professional behaviour, is the differentiation of therapeutic styles across treatment stages. This approach is a variation of, but consistent with, the trans-theoretical model of change [21] which differentiates people’s readiness to change into various stages. Different methods (e.g. motivational interviewing) are used to prevent the usual mental health treatment ‘script’. In this script, the professional is the one who looks for problems in the patient and suggests improvements of his or her behaviour, while the patient is a passive recipient of help. In the second stage of ICPT, motivational interviewing is used to do enable systematic goal-setting. After an initial open question to focus the patient on the future, a widely used tool to assess care needs [22] is used, after which specific goals are jointly formulated. This careful process of mutual goal setting seeks to avoid common pitfalls: the patient feeling that treatment goals are forced upon him or her, and the professional feeling that urgent patient needs (e.g. financial problems) have not come under discussion. In the third stage of ICPT, three different goal-oriented methods are used to improve personal and social functioning. Practical case management, motivational interviewing and aspects of cognitive behaviour therapy may be used. This third stage of ICPT, which may not be reached by all patients, aims to offer practical help after goal-setting in stage two has been concluded.IV.**Application of feedback forms:** In ICPT, both professional and patient fill out a form about the session they have just had. Both rate items on the Session Rating Scale [23], thereby informing one another on their (dis) content with the working alliance. In addition, professionals score in which stage of the treatment contact this session could be located, as well as which methods were used, if treatment goals were discussed, and a number of other elements, using the ICPT-form and scoring form after each session [9]. Patients, on the other hand, rate their own input in the session’s content. By these means, both parties are delegated responsibility for the working alliance and their substantive input in the session.V.**Supervision:** Every two weeks, a team-wise supervision takes place in which a treatment situation of two different professionals is jointly analysed. We use a brief version of a supervision protocol that has been developed and evaluated in Dutch long-term mental health care [24].

#### CAU

Care as usual (CAU) currently is a low-structured treatment/care: biweekly contacts with a nurse, social worker or occupational therapist, in which daily issues are discussed [7]. This CAU lacks an empirical and theoretical base and may foster dependence and repeated crises through its ad-hoc character [25] and lack of clear aims [26]. Without a clear frame, this CAU turns into – politically incorrect – ‘pampering and dithering , reinforcing patients’ dependency and high care use [27]. The present CAU is offered by non-academically trained professionals (e.g. nurses and social workers) who have always relied on practical, day-to-day interventions in acute circumstances (e.g. locked units or psychosocial crises).

Although these generalizing statements do not apply to all of these professionals, most – if not all – of them feel that they lack a solid theoretical base from which to understand the disorder, its long (er) term character, and possible treatment.

Participating professionals in the experimental condition will receive a 4-day training in ICPT over 4 weeks’ time. The ICPT-training has been piloted twice before, and consists of the following elements: (1) theoretical overview (4 hours), (2) generic ICPT-skills, e.g. agenda setting (4 hours), (3) relationship management skills (8 hours), (3) motivational interviewing and goal setting skills (8 hours), (4) case-management skills and behavioural analysis skills (4 hours) and skills to discharge patients to a lower form of care. It combines lectures, group discussions, one-on-one and group-wise role-playing, homework assignments, and self-study of provided literature. Substantial effort is put in tailoring the training program to the needs and competencies of the participants. Some of the ICPT-methods for patients with non-psychotic disorders are aimed at Master-level professionals (e.g. Cognitive Behavioural Therapy), whereas the participating professionals – the key professionals of patients and also those intended to carry out ICPT –usually have Bachelor-level qualifications. Tailoring will be done by inviting specialists with extensive experience with both the target group of professionals, and the method to be taught. In following group-wise supervision sessions ICPT-skills will be practiced, and cases will be discussed.

### Measurements

#### Demographic variables

At baseline, participants complete questions concerning living situation, marital status, education, income and working situation.

#### Baseline

Table 1 schematically shows the instruments used in the study. A structured diagnostic interview about the patient’s diagnosis is the first step in the baseline assessment. Axis I psychiatric disorders will be assessed by use of the electronic version of the MINI Plus (Mini Neuro-psychiatric Interview) [28]. The MINI Plus is the briefest full psychiatric interview available and takes, dependent on the number of disorders, between 15 and 45 minutes. A 10-item screening instrument will be used to assess whether a full structured diagnostic interview for Axis II psychiatric disorders is required. The Standardised Assessment of Personality – Abbreviated Scale - Self Report (SAPAS-SR) has been found one of the briefest, most sensitive and specific screening instruments for Axis II disorders [29]. We expect about 50% positive screens in this secondary care sample. A positive screen will be followed by the Structured Interview for DSM-IV (SIDP-IV) [30]. The SIDP-IV is a widely used semi-structured interview with good psychometric properties.

**Table 1 Tab1:** **Measuring instruments**

Instrument	Measuring moments			
	T0(baseline)	T1(6 months)	T2(12 months)	T3(18 months)
**Filled in by researcher**				
Demographic questionnaire	X	X	X	X
MINI Plus	X			
SAPAS-SR	X			
SIDP-IV (when SAPAS-SR positive)	X			
CANSAS (Patient)	X	X	X	X
SNM	X	X	X	X
**Filled in by patient**				
OQ-45.2	X	X	X	X
MANSA	X	X	X	X
IMR (Patient)	X	X	X	X
EQ-5D	X	X	X	X
TiC-P	X	X	X	X
STAR (Patient)	X	X	X	X
**Filled in by professional**				
DDPRQ	X	X	X	X
HONOS	X	X	X	X
CANSAS (Professional)	X	X	X	X
IMR (professional)	X	X	X	X
STAR (professional)	X	X	X	X

All outcome measures (MANSA; HONOS; IMR; EQ-5D; OQ45; TiC-P; STAR; DDPRQ; CANSAS; SNM) will be assessed at baseline, and at 6 months, 12 months and 18 months. Referral to lower intensive services will be assessed at the 12-month and 18-month measurement.

### Primary outcome

#### Quality of life

Quality of life is measured on participant level with the MANSA [31]. The MANSA (Manchester Short Assessment of Quality of Life) is the single most used quality of life instrument for patients with severe mental illness. It is a 16-item patient-rated instrument with good psychometric properties.

### Secondary outcomes

#### Quality of life

The EQ-5D (EuroQol 5D) [32] is a patient-rated measurement of health-related quality of life, providing a generic measure of health for clinical and economic appraisal. It is applicable to a wide range of health conditions and treatments, and provides a single index value for health status that can be used in the clinical and economic evaluation of health care. It is a 5-item patient-rated instrument with good psychometric properties that allows the calculation of QALY’s and DALY’s.

### General mental health

The HONOS (Health of the Nation Outcome Scale) is a 12-item professional-rated instrument to assess general mental health in predominantly SMI-patients [33] with good psychometric properties and a mean duration of 10 minutes [34].

### Treatment

The OQ-45 (Outcome Questionnaire) a 45-item instrument which assesses treatment outcome, mostly in terms of symptom reduction [35] with very good psychometric properties and a mean duration of 10 minutes [36].

### Recovery

The Illness Management and Recovery (IMR) [37] scale was created to measure recovery outcomes produced by the IMR program. However, many other mental health care programs are now designed to impact recovery-oriented outcomes, and the IMR has been identified as a potentially valuable measure of recovery-oriented mental health outcomes in general. Psychometric properties were moderate and the scale has a mean duration of 10 minutes.

### Costs

The Tic-P (Trimbos/iMTA questionnaire for Costs associated with Psychiatric Illness) [38] measures direct costs of medical treatments such as the number of contacts with psychiatric services, the GP and multiple other care providers, psychometric properties are unknown and has a mean duration of 10 minutes.

